### Data and Safety Monitoring

An independent data safety and monitoring board (DSMB) is implemented and will be informed about adverse events (AE), potentially related to the use of the device, any serious adverse events (SAE), device deficiencies, and the progress of the trial. (S)AEs follow the definition of ISO 14155:2020 3.2 and 3.45. All SAE and device deficiencies will be reported to the Sponsor within 24 h. The Sponsor is obliged to report to the former to the Competent Ethics Committee (Commission cantonale d'éthique de la Recherche sur l'être humain in Vaud) and the second one to Competent Authority (Swissmedics) within 7 calendar days. The trial will be stopped if there is a medically relevant increase in major, unexpected AE with the intervention compared with the waiting group. Moreover, the study has implemented a monitoring plan involving 10 site visits, including the site-initiation and close-out visits. The monitoring will cover the conduct of the study, the completeness of files and documents as well as data security, (S)AE and device deficiencies.

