### Study Procedure

All thirty planned patients will receive a cumulative neurotechnologies-based intervention: (1) Interventional phase 1 (IP1) uses a BCI to control supra-motor threshold FES for the upper-limb and a hand exoskeleton for flexion and extension of the fingers with arm support; (2) Interventional phase 2 (IP2) adds tDCS to IP1.

The duration of both interventions is tailored for each patient and is determined according to improvement monitored through a short version of the FM-UE (sFM-UE) (35), consisting of 54 points excluding reflexes and coordination items. This short FM-UE is assessed every second session of intervention. The patient is considered to have no further prospect of recovery when no improvement in terms of sFM-UE is seen in the current session (Si), defined by:

(1)
$$\begin{array}{r} {\text{sFMUE}}_{\text{Si}}\;\leq \text{ median}\left({\text{sFMUE}}_{\text{Si}-2},\;{\text{sFMUE}}_{\text{Si}-4},\;{\text{sFMUE}}_{\text{Si}-6}\right) \end{array}$$

When this condition is met, the intervention changes to a second stage and the same procedures take place to determine the end of *IP2*. A minimum of 11 sessions per intervention is provided and equation (1) is thus applied from the eleventh session of both phases. The session counting of *IP1* begins when the patient can govern the BCI (i.e., reaching 70% of accuracy in offline model validation); this choice is made to have a similar amount of *valid* therapy sessions in the two interventional phases. In addition to the therapies, every subject participates in three multimodal assessment visits: before *IP1* (T0), at the change to the second interventional phase (T1), and at the end of *IP2* (T2). A follow-up visit is scheduled 3 months after the end of *IP2*. The full procedure can be seen in Figure 1. Visits and interventions are conducted at the centers, in our laboratory spaces. Only screening and observation visits may be done at the patient's place of residence.

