#### Observational Period

Given the absence of a control group, 10 randomized patients will also do, in addition to the standard protocol, a 3-month observational period prior to the intervention to further validate that the targeted population is in the plateau phase of recovery with a stable level of motor impairment, as suggested in the literature.

Upon recruitment, patients are randomized with a one-to-two distribution into the waiting or the starting group. The waiting group (*n* = 10) corresponds to the patients doing first the observational period and then starting the treatment phase; the starting group (*n* = 20) will directly begin with the treatment phase. The waiting group undergoes an observational period of 3 months prior to beginning the treatment, whereas the starting group begins the treatment immediately. Once the intervention starts, both groups continue the procedure in the same way and receive the same treatment described in the previous paragraphs.

The assignment of patients (waiting or starting group) is performed per center and takes age group (before 50, between 50 and 65, and over 65) and side of impairment into account (53).

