### Statistics

To evaluate if significant motor improvement of the upper-limb is achieved, the FM-UE scores of all the 30 patients will be compared between the final (T2) and the initial (T0) evaluation visits: we will use a two-tail paired Wilcoxon Signed Rank test, with the probability value set at 0.05. The null hypothesis is H0 = “FM-UE scores at T2 and FM-UE scores at T0 follow the same distribution”, H1 = “FM-UE scores at T2 do not follow the same distributions of scores at T0; the distributions are significantly different”. H0 will be rejected if a *p-*value < 0.05 is obtained. This evaluation will be considered together with the expected four-point improvement on average.

To assess if the observed changes in the FM-UE are long-lasting, we will compare with the same test (Wilcoxon Signed Rank, alpha = 0.05) the FM-UE scores at T2 with those acquired at the follow-up (3 months after T2). Another related secondary outcome regards the validation of motor function stability of chronic stroke patients (i.e., no FM-UE improvement during the observation period). We will use a Kruskal-Wallis test with alpha at 0.05 to investigate differences in the FM-UE scores at the three time points of the observation period. We do not expect to reject the null hypothesis for which the three groups are said to come from the same distribution.

Among the most important secondary outcomes is safety and feasibility; for these, descriptive statistics will be provided. One major safety outcome is incidence of epileptic seizures during the intervention period with tDCS, as well as other SAEs. Furthermore, feasibility will be determined by the drop-out rate, usually in clinical trials set to up to 20%.

Important exploratory analyses will focus on the difference between the two interventional phases; such investigation might give an insight on the role of tDCS in the rehabilitation. To test the effect of dose and intervention type on the FM-UE we will use a mixed effects linear model with random effect of subject and fixed effects of session, intervention type and the interaction of the two. If significant results will be observed, we can then build on this initial model by adding more independent variables such as lesion location and time post-stroke. Other analyses will correlate the multimodal data acquired during the three full evaluations (T0, T1, T2), such as corticospinal tract integrity and the TMS evoked potential, with the clinical scales.

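### Non-serious adverse events reach the DSMB only if potentially device-related, so major but non-serious background events can enter the intervention-versus-waiting comparison from one side only

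*Protocol article*

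**What the plan says.** Three statements matter, two of them in one section.

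- **What the DSMB receives** (Data and Safety Monitoring): the board "will be informed about adverse events (AE), potentially related to the use of the device, any serious adverse events (SAE), device deficiencies", together with the progress of the trial. Relatedness to the device qualifies the adverse events. The word *any* stands before SAEs, so these carry no such condition.
- **The comparison** (same section): "The trial will be stopped if there is a medically relevant increase in major, unexpected AE with the intervention compared with the waiting group". The rule is worded in terms of major, unexpected AEs, although the section uses the terms SAE and (S)AE elsewhere. Major is not defined.
- **The comparator** (Observational Period): "The waiting group undergoes an observational period of 3 months prior to beginning the treatment, whereas the starting group begins the treatment immediately". This group has 10 patients.

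On SAEs the section adds: "All SAE and device deficiencies will be reported to the Sponsor within 24 h". That sentence has no restriction by group or by relatedness.

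**The concern.** A comparison of harm between two periods needs events that are counted by the same rule in both. Here, admission of a non-serious event to the board's information depends on whether it may be related to a device that only one of the two periods uses. A background event of severe chronic stroke can be judged potentially related when it occurs during the intervention and so be reported. The same event during waiting cannot meet that condition.

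The waiting group is the trial's only untreated comparator. If background events from it do not reach the board, it cannot show which major non-serious events would have occurred anyway. An apparent excess under intervention might then come partly from the reporting rule. Equally, a real excess might be dismissed as an artefact of that rule.

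**Working it through.** The plan gives no adverse event rate, no numerical boundary and no definition of major, so there is no figure to reproduce. The check is of the text, followed by an illustration on assumed values.

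**Step 1. Which events reach the DSMB, by period, on the literal wording**

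| Event | Observational period (no device) | Intervention period |
|---|---|---|
| SAE, any cause | sent | sent |
| Non-serious AE, judged potentially device-related | cannot occur | sent |
| Non-serious AE, not judged device-related | not sent | not sent |

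The SAE row is symmetric. For non-serious events, the number sent from the waiting period is 0 whatever the true number.

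**Step 2. Which of these events the comparison concerns**

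The rule covers only major, unexpected AEs. The asymmetry bears on it only for events that are major and non-serious. If every major event is also serious, only the SAE row applies and there is no distortion.

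**Step 3. Illustration with no true harm**

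Assumptions, none of them in the document:

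- the true rate λ of major, unexpected AEs per person-time is the same in both periods;
- a share s of these events is non-serious;
- a fraction p of the non-serious ones is judged potentially device-related during the intervention.

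Rate reaching the DSMB from waiting: λ(1 − s).
Rate reaching it from the intervention: λ(1 − s + sp).
Reported rate ratio: (1 − s + sp)/(1 − s).

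| s | p = 0.25 | p = 0.5 | p = 1 |
|---|---|---|---|
| 0 | 1.00 | 1.00 | 1.00 |
| 0.1 | 0.925/0.9 = 1.03 | 0.95/0.9 = 1.06 | 1/0.9 = 1.11 |
| 0.3 | 0.775/0.7 = 1.11 | 0.85/0.7 = 1.21 | 1/0.7 = 1.43 |
| 0.5 | 0.625/0.5 = 1.25 | 0.75/0.5 = 1.50 | 1/0.5 = 2.00 |

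The true ratio is 1 throughout. The table shows direction and sensitivity. It does not estimate what will happen in this trial.

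**Step 4. What could go unseen in the waiting group**

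Assume that 5% to 40% of patients have some non-serious AE in 3 months. Among 10 waiting patients, 10 × 0.05 = 0.5 to 10 × 0.40 = 4.0 would be expected to have one. The chance of at least one such patient is 1 − 0.95^10 = 0.40 to 1 − 0.60^10 = 0.99. The board would be told of none. Major events would be a subset of these, possibly an empty one.

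**The case against.** **The affected class may be empty.** All SAEs pass unfiltered from both periods, and major, unexpected events may all be serious. This stands as a limit on the size of the problem. It does not remove it, because the section has the term SAE available and uses a different, undefined one for the stopping comparison. On this wording, a major non-serious class is not excluded.

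**The comparison may not rest on the DSMB's information.** The section limits what is sent to the board, not what is collected. It names neither the body that applies the rule nor the data used, and site monitoring covers (S)AE without a relatedness condition. A reader might infer that the whole comparison rests on a waiting-group count that is zero by construction. The document does not say that. It does support a narrower statement: the only independent safety body described is not given the non-serious events that such a comparison would need from the waiting side.

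**Zero can be the right count.** For an event that the device truly causes, no occurrences in unexposed patients is correct. The filter also removes unrelated events during treatment. This stands: the distortion comes only from background events that are judged potentially related under treatment.

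**The wording is ambiguous.** The comma after the AE abbreviation leaves some doubt about whether relatedness restricts the adverse events. Restriction is the natural reading, given the contrast with the unqualified SAEs. If all AEs were meant, the sentence still needs correcting.

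**Contact frequency.** A reader might add that treated patients are seen far more often, so more of their events would be noticed. The document does not support building on this. Nothing says that AEs are collected only at visits, a raw count of visits ignores the different lengths of the periods, and a journal article ordinarily leaves methods of eliciting events to the full protocol.

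**Conclusion.** The point holds in a limited form. Data and Safety Monitoring states both a relatedness condition on the non-serious AEs sent to the DSMB and an intervention-versus-waiting comparison that is not confined to SAEs. The two do not fit, because the observational period has no device exposure. This is a conflict between two stated rules, not a complaint about missing detail.

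Its reach is restricted to major, non-serious background events as reported to the DSMB. The size cannot be determined from the document. It is nil if major means serious, and the reported ratios of 1.03 to 2.0 rest wholly on assumed values of s and p. The conclusion also assumes the restrictive reading of the relatedness phrase and that the DSMB's information plays a part in the comparison. A reader might conclude that the board would necessarily see a false excess, or that safety monitoring as a whole is invalid. Neither follows, since SAE reporting is symmetric and the affected class is undefined.

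**What to change.** Reconcile the two sentences in Data and Safety Monitoring:

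1. State that the adverse events entering the intervention-versus-waiting comparison are reported to the DSMB from both the observational and the intervention periods, irrespective of attributed relatedness to the device.
2. Say whether major includes events that are not serious.
3. Keep device-related AEs and device deficiencies as a separate listing that is not used for the comparison.

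If the comparison is meant to draw on a source other than the DSMB's information, naming that source would resolve the data-flow question.

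The cost is a change of wording in the protocol or the DSMB charter and a longer AE listing for the board, which would now include unrelated non-serious events. No stopping threshold or clinical rule is proposed here.

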## Discussion

The AVANCER protocol proposes two important novelties to enhance neurorehabilitation and bring forward the current therapeutic options in severely impaired stroke patients: a combination of neurotechnologies and a highly personalized treatment intervention. We believe that the present interventional strategy, combining several neurotechnologies in a personalized fashion, will have a large potential to be translated into clinical settings, if successful. We hypothesize that the personalized, sequential multi-technology-based interventions will further support behavioral restitution of impaired functions in this group of patients with limited treatment options in the chronic stage. We expect that this treatment will mechanistically not only act on brain plasticity and functional reorganization (BCI and tDCS), but will also show beneficial effects on the musculoskeletal system in a synergistical way. Specifically, with the support of FES and exoskeleton, a multitude of repetitive upper extremity movements can be performed by the patient allowing full upper limb movements (not possible in these patients without the present interventional strategy). Such movements are performed thanks to an exoskeleton that passively extends and flexes the fingers and supra-motor threshold FES on seven muscles. The continuous movements might help decreasing possible spasticity, atrophy and hopefully reverse some of the changes that resulted from months of no movements performed.

Regarding brain plasticity, previous BCI studies have reported cortical reorganization alongside the clinical motor improvement (19, 20, 63). These results are thought to be partly due to the brain engagement needed for the BCI to work (64) and we hypothesize that the underlying plastic changes can further be enhanced with tDCS, which was reported to have a positive effect on the strength of event related desynchronizations (65–67) and motor outcome (68, 69). We assume that behavioral restitution of function, induced by the combined neurotechnology approach will go alongside with cortical reorganization processes, which we plan to capture by a multimodal evaluation by means of (f)MRI, DTI and TMS-EEG related outcome measures. These combined measures will allow to show if the present approach can induce changes on multiple levels of the phenomenological model (70) underlying recovery after stroke.

The study outcome is evaluated with the 66-point FM-UE, currently seen as the gold standard measure for motor impairment and function of the upper extremity. Following the suggestions of the SRRR (28), we also instrument this scale with EMG and IMUs to gather further data such as kinematic information, able to better characterize movement quality and functional changes.

The expected primary outcome is a four-point improvement in the FM-UE on average across patients and this is set to be the MCID in this study. Although this is lower than previously suggested (59), it is of note that this suggestion was based on less impaired stroke patients in the acute phase post-stroke, we believe it is an appropriate MCID for the present population of severely impaired patients (60, 61).

The FM-UE, together with the other longitudinal assessed scales and neural correlates will provide important data for understanding the effects of the intervention at a group level and for identifying patients who will potentially benefit from this intervention.

## Summary and Conclusion

The experimental and technological set-up of the present clinical trial, where an exoskeleton, multi-electrode FES, BCI and non-invasive brain stimulation are used together in a personalized fashion in a clinical trial aimed at improving upper limb impairment in severely affected stroke patients with so far very limited treatment options. We propose a personalized, patient-tailored interventional strategy, where the targeted population is provided with advanced neurotechnologies to achieve maximized interventional effects, without restraining with one type of intervention, but rather have an add-on, synergistic continuous therapy following the individual needs and improvement. We aim to achieve motor improvement due to the central engagement given by BCI and later enhanced by tDCS and the peripheral activation of natural afferent and efferent pathways by the concomitant action of actuators and further enriched through the performance of a variety of functional exercises. The trial will allow the collection of longitudinal multi-modal neurophysiological data constituting a precious dataset for studying motor recovery in the target population.

## Ethics Statement

This study has been approved by the Ethics Committee of the Canton of Vaud (No. 2019-00094) and Swissmedic (No. 10000577). The patients/participants provided their written informed consent to participate in this study.

